### Intervention

Preoperatively all patients will undergo: blood tests (complete blood count, liver and renal function, coagulation profile, serum *α*-fetoprotein level, and hepatitis B and C serology); radiological imaging (chest X-ray, CT scan, or MRI to assess tumour size, number, location, and image-guided volumetry of future liver remnant); ICG-15 test^19^; and quality of life assessment using a Chinese version of the Functional Assessment of Cancer Therapy-General (FACT-G) questionnaires.

All patients will receive prophylactic antibiotics (Augmentin (amoxicillin + clavulanate) (GlaxoSmithKline) 1.2 g intravenously for one dose or levofloxacin (Daiichi Sankyo) 500 mg intravenously for one dose in case of penicillin allergy) and proton pump inhibitor (pantoprazole (Takeda) 20 mg intravenously for one dose). The surgical intervention will be performed under general anaesthesia.

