### Outcomes

#### Primary outcome

The primary outcome is 2-year recurrence-free survival.

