### Sample size

Based on a reported 2-year recurrence-free survival rate of 72 per cent after OMH^12^ and an expected 88 per cent after LMH according to a previously reported series^8^, 150 patients need to be recruited to each arm to demonstrate a statistically significant difference with 80 per cent power at the 0.050 level of two-sided significant difference between LMH and OMH^24^. Allowing a 10 per cent dropout rate, 165 patients will be recruited in each arm. This sample size will allow detection of a reduction of 2-year tumour recurrence from 50 per cent in the OMH group to 30 per cent in the LMH group with a similar power and level of significance. Secondary outcomes will be interpreted for hypothesis-generating only.

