### Randomization

Preoperative randomization will be adopted on the day of admission. A total of 330 subjects will be allocated 1:1 to either the LMH group or the OMH group. The randomization schedule will be generated by the Clinical Trials Centre (CTC) of the principal investigator’s centre, prior to the start of the study. Stratified block randomization (block size of 10) will be used to ensure treatment allocation in equal proportions at each centre. The randomization list will be kept in a set of tamper-evident envelopes. The envelopes will be identical and sealed. The trial identifier with a sequential number will be printed on each envelope. Envelopes will be unsealed to reveal the allocation treatment 1 day prior to surgery.

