### Statistical plan

The 2-year recurrence-free survival (primary outcome) and overall survival will be evaluated by Kaplan–Meier method and compared by the log rank test. Other secondary outcomes will be compared using the chi-squared test or Fisher’s exact test for categorical variables, and the Mann–Whitney *U* test for continuous variables. *P* < 0.050 will be considered statistically significant. Statistical analysis will be performed using SPSS version 11.0 (SPSS Inc., Chicago, IL, USA).

All clinical data including patients’ demographics, operative details, tumour characteristics, and clinical outcome measure will be collected and centralized at the principal investigator’s centre using a password-protected web-based system to ensure confidentiality of personal information. Continuous clinical data monitoring will be performed by the principal investigator and co-investigators with the help of biostatisticians and research assistants. The data set will be kept confidential until the publication of trial results.

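### The primary log-rank test is valid but ignores AFP, tumour size, tumour number and centre, all already on record; using them would add a little power at no data cost

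*Protocol article*

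**What the plan says.** Protocol article, Primary outcome: "The primary outcome is 2-year recurrence-free survival". Statistical plan: this outcome and overall survival "will be evaluated by Kaplan–Meier method and compared by the log rank test". No covariate, model or stratum is named for that comparison.

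Intervention: before surgery all patients have blood tests that include AFP, and imaging by chest X-ray, CT or "MRI to assess tumour size, number, location, and image-guided volumetry of future liver remnant". Table 1 places the hepatectomy work-up at enrolment, one month before allocation. The eligibility limit of 8 cm on total tumour diameter also means that size and nodule count must be known before a patient enters. As extracted, the AFP row of Table 1 has marks only in follow-up columns. That may be a table-reading fault, and the Intervention section is explicit that AFP is measured preoperatively.

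Randomization: stratified blocks of 10 "will be used to ensure treatment allocation in equal proportions at each centre". Centre is the only stratification factor stated.

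Sample size: the open-surgery rate is "Based on a reported 2-year recurrence-free survival rate of 72 per cent after OMH", with "an expected 88 per cent after LMH according to a previously reported series". From these, "150 patients need to be recruited to each arm" for "80 per cent power at the 0.050 level of two-sided significant difference".

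**The concern.** AFP, tumour size and tumour number are plausible predictors of recurrence and cost nothing more to obtain. If they are prognostic, a test that uses them is more powerful than one that does not, with the same patients and visits. Centre is built into the allocation but does not appear in the test. Tumour burden is balanced only by chance, and the named test does not correct for an imbalance that happens to arise. What is at stake is a modest amount of power and a result that is easier to defend if the arms differ at baseline. The validity of the trial is not in question.

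**Working it through.** **1. The plan's own figure.** With 72% v 88%, two-sided 0.05 and 80% power, the usual two-proportion formula is

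n = [1.96·√(2·0.80·0.20) + 0.8416·√(0.72·0.28 + 0.88·0.12)]² / 0.16² = (1.1087 + 0.4665)² / 0.0256 ≈ 97 per arm (110 with continuity correction).

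The stated 150 is not reproduced. That mismatch is a separate matter, but it sets the starting point here. With 150 per arm, power is 93.8% by proportions. By events, 150 × 0.28 + 150 × 0.12 = 60 and HR = ln 0.88 / ln 0.72 = 0.389, so z = √(60/4) × 0.944 − 1.96 = 1.70, which is 95.5% power. For the second scenario (recurrence 50% v 30%), the same methods give 94.6% and 95.3%.

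**2. Gain from adjustment.** The article gives no prognostic strength, so it is an assumption: the three baseline values form a normal log-hazard score with SD 0.3, 0.5 or 0.7. Trials were simulated with 150 per arm, exponential hazards calibrated so that the marginal 2-year rates stay as stated, and censoring at 24 months. The unadjusted test (log-rank or Cox Wald) was compared with a Cox Wald test adjusted for the score. The rates 82% and 62% are assumed smaller effects and are not in the article.

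| 2-year RFS, open v laparoscopic | SD | Trials | Unadjusted | Adjusted | Gain (points) |
|---|---|---|---|---|---|
| 72 v 88 (planned) | 0.3 | 2,000 | 94.1% | 94.1% | 0.0 |
| 72 v 88 (planned) | 0.5 | 2,000 | 94.2% | 94.7% | 0.5 |
| 72 v 88 (planned) | 0.5 | 5,000 | 94.0% | 95.2% | 1.2 |
| 50 v 70 (second scenario) | 0.5 | 2,000 | 96.5% | 97.8% | 1.3 |
| 72 v 82 (assumed) | 0.3 | 5,000 | 53.4% | 54.9% | 1.5 |
| 72 v 82 (assumed) | 0.3 | 2,000 | 54.4% | 55.1% | 0.7 |
| 72 v 82 (assumed) | 0.5 | 5,000 | 54.0% | 57.2% | 3.2 |
| 72 v 82 (assumed) | 0.5 | 2,000 | 53.3% | 55.2% | 1.9 |
| 72 v 82 (assumed) | 0.7 | 5,000 | 55.1% | 60.9% | 5.8 |
| 72 v 82 (assumed) | 0.7 | 4,000 | 52.5% | 58.8% | 6.3 |
| 50 v 62 (assumed) | 0.5 | 5,000 | 57.0% | 62.0% | 5.0 |

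The Monte Carlo standard error of each power is about 0.5 to 1 point. Paired gains are more precise, with an error of 0.2 to 0.7 points in the 4,000-trial run. Type I error was 4.8% unadjusted and 4.9% adjusted. With stronger scores than assumed, the gain at 72 v 88 is 2.0 points (SD 0.8) and 3.6 points (SD 1.0). At 72 v 82 and SD 1.0 it is 10.5 points (54.9% to 65.4%).

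**3. The gain as patients.** The ratio [(1.96 + z_adj)/(1.96 + z_unadj)]² for 72 v 82 in the 5,000-trial runs is:
- SD 0.3: (2.083/2.045)² ≈ 1.04
- SD 0.5: (2.142/2.060)² ≈ 1.08
- SD 0.7: (2.237/2.088)² ≈ 1.15

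That is the equivalent of about 4%, 8% and 15% more patients.

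**4. Chance imbalance.** With 150 per arm, the mean standardised score differs between arms by more than 1.96 × √(2/150) = 0.23 SD in 1 trial in 20. At SD 0.5 this shifts the log hazard ratio by about 0.5 × 0.23 = 0.11. For 72 v 82 the log hazard ratio is ln(ln 0.82 / ln 0.72) = −0.50, so the shift is about a fifth of the effect.

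The simulations did not include centre, so no size is claimed for stratifying by it.

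**The case against.** The strongest objection is that nothing is wrong. An unadjusted log-rank test in a randomised trial is valid, it contradicts nothing else in the article, and adjusted models may appear in an analysis plan that is not shown. This stands in part: the point concerns efficiency only. It survives because the article itself fixes the primary test, so an adjusted analysis elsewhere could only be supportive.

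Second, almost nothing is lost at the trial's own rates, and the larger gains rest on effects and prognostic strengths that the article does not give. This also stands. The eligibility limits (8 cm, single lobe, no radiological vascular invasion, Child A) narrow the spread of risk, which favours the lower end of the assumed SD range. The Discussion says that matched comparisons were comparable, but those groups had fewer than 40 patients each. They leave a smaller true effect possible without establishing it. A trial with about 55% power would also remain underpowered after adjustment.

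A reader might infer that the plan throws away power for nothing. The documents do not support that: the loss at the planned effect is about a point at most for weak to moderate covariates, and adjustment has a price in modelling assumptions.

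A reader might also infer that omitting covariates biases the result towards no difference. That confuses two targets. The conditional hazard ratio lies further from 1 than the marginal one (for 72% v 88%, 0.379 at SD 0.5 against 0.389), but the unadjusted test is not biased and the Kaplan–Meier 2-year rates are unaffected. Chance imbalance is likewise already covered, on average, by the type I error rate; adjustment helps in the particular trial where it occurs.

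**Conclusion.** The point holds as a low-cost improvement and not as an error. The primary test leaves unused the baseline AFP, tumour size and tumour number collected in every patient, and also the centre stratum. With 150 per arm and an assumed score SD of 0.3 to 0.7, the gain is about 0 to 1 point at 72% v 88% for SD up to 0.5, from a power of about 94%. It is about 1 to 6 points at an assumed 72% v 82%. Larger gains need stronger covariates than assumed here. The direction is secure if the covariates are prognostic; the size depends on prognostic strength and on the true effect, neither of which the article can settle.

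**What to change.** In the Statistical plan, name one primary test: a centre-stratified, covariate-adjusted log-rank test, specified as the score test for treatment in a Cox model stratified by centre. The covariates are log AFP, total tumour diameter in cm and single v multiple nodules, each at its last value recorded before allocation. Fix their form, and the handling of any missing baseline value, before outcomes by arm are seen. Because the article plans interim analyses at four-monthly investigator meetings, record the date of the change relative to any comparison by arm.

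Keep the Kaplan–Meier 2-year rates and the unadjusted log-rank test as supportive analyses, and state that any adjusted hazard ratio is conditional on the covariates.

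The cost is a few sentences in the plan, with no new patients, visits or data. The price is a modelling assumption about covariate form and a hazard ratio that must be labelled as conditional.

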#### Secondary outcomes

These include 30-day, 90-day, and in-hospital mortality, postoperative complications, quality of life, time to functional recovery, 2-year overall survival, 5-year overall survival, and recurrence-free survival. Surgical stress-related cytokines serum interleukin 6 (IL-6) and immunosuppressive acidic protein (IAP) will be measured before surgery and on postoperative days 1 and 7. Measurement of IL-6 and IAP levels will be performed by immunoassay using commercially available kits (MILLIPLEX^®^ MAP Human Cytokine/Chemokine Magnetic Bead Panel, Merck Ltd, Rahway, NJ, USA).

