### Measurements

Intraoperative: operative time (measured from time of skin incision to wound suturing); blood loss; blood transfusion volumes and other blood products (platelet concentrate, fresh frozen plasma); intraoperative major events (hypotension for greater than 20 min and use of inotropes); and laparoscopic to open conversion. The conversion is defined as the change of surgical approach during the resection phase of major hepatectomy, when the operating surgeon encounters technical difficulty. Patients undergoing conversion will be included in the laparoscopic group and be analysed on an ‘intention-to-treat’ basis.

Postoperative: liver biochemistry and coagulation profile on postoperative days 1, 3, 7, and day of discharge; postoperative morbidities according to Clavien–Dindo classification^22^; 30-day, 90-day, and in-hospital mortality; length of ICU and hospital stay; hospital readmission (90 days after discharge); and time to functional recovery (defined as independently mobile at the preoperative level, sufficient pain control with oral medication alone, ability to maintain at least 50 per cent daily caloric intake, no intravenous fluid administration, and no clinical signs of infection)^23^.

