### Follow-up

No adjuvant treatment will be used after surgery. All patients will be followed up every 3–6 months for up to 5 years after operation. Follow-up assessment will include: liver function (clinical assessment of Child’s grade, complete blood count, liver, and coagulation profile); recurrence (based on serum *α*-fetoprotein level, chest X-ray, and CT scan of abdomen with contrast); and quality of life (FACT-G questionnaires).

Patients with intrahepatic recurrence will be managed by laparoscopic re-resection for the LMH group or open re-resection for the OMH group when considered feasible. For patients in whom re-resection is not possible, thermal ablation, transarterial chemoembolization, or salvage liver transplant will be offered according to the decision of the multidisciplinary team.

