## Discussion

The aim of the AP-LAPO trial is to test the hypothesis that LMH is associated with reduced surgical stress and immunosuppression compared with OMH resulting in lower tumour recurrence rates and better survival.

OMH for HCC is associated with major morbidity of up to 40 per cent in high-volume centres^25–28^ as well as a high tumour recurrence rate. The 3-year recurrence rate has been reported to be greater than 50 per cent^7,29^ with most of these recurrences occurring in the liver remnant. Manipulation of the tumour during OMH along with postoperative immunosuppression induced by surgical stress have been suggested as factors that may increase risks of recurrence in the liver remnant^30^.

Recent series have proven the feasibility and safety of LMH for HCC^17^. The conversion and morbidity rates are around 10 per cent. Fewer wound and chest complications and shorter hospital stays are seen after LMH compared with OMH^10^. An animal study has shown that LMH results in less surgical stress and immunosuppression than OMH^9^. Theoretically, laparoscopic instrumentation causes less manipulation of the tumour that might limit cancer-cell dissemination, reducing tumour recurrence and prolonging survival. The reduced immunosuppression might also influence recurrence rates and survival in LMH. This theory is supported by a recent meta-analysis based on reconstructed time-to-event data^11^.

To date, only retrospective studies using propensity score matching have compared LMH and OMH^8,12^. Sample sizes were small (less than 40) in each matched group and the reported 2-year overall and recurrence-free survival were comparable between OMH and LMH. This trial aims to provide high-level evidence to see if there is added value of laparoscopic surgery in the treatment of patients with HCC.

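### The Mann–Whitney test fixed for all continuous secondary outcomes has no place for baseline value or centre, and time to functional recovery has no rank for patients who die or never recover

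*Protocol article*

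**What the plan says.** In the Protocol article, the Statistical plan reserves time-to-event methods for two outcomes: recurrence-free survival and "overall survival will be evaluated by Kaplan–Meier method and compared by the log rank test". The remaining secondary outcomes get a chi-squared or Fisher test if categorical and the "Mann–Whitney *U* test for continuous variables". Quality of life, the two cytokines and time to functional recovery therefore all fall under the rank test.

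The data available for these outcomes are richer than one value per patient:

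- **Cytokines.** Under Secondary outcomes, IL-6 and IAP "will be measured before surgery and on postoperative days 1 and 7".
- **FACT-G.** The Intervention section lists, before surgery, "quality of life assessment using a Chinese version of the Functional Assessment of Cancer Therapy-General (FACT-G) questionnaires", and Table 1 marks the assessment at enrolment. The Follow-up section repeats the questionnaire: "All patients will be followed up every 3–6 months for up to 5 years after operation".
- **Centre.** The Randomization section stratifies by centre, in blocks of 10.
- **Functional recovery.** The Measurements section defines the outcome by several criteria that must all be met, beginning "time to functional recovery (defined as independently mobile at the preoperative level". It does not say what value a patient has who dies first or never meets them all.

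Two other statements bear on the point. The Sample size section limits secondary outcomes to generating hypotheses. The Interim analyses section commits the final analysis to intention to treat.

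**The concern.** A two-sample Mann–Whitney test takes one number per patient and a group label. It cannot use the pre-surgery value as a covariate, combine several visits or account for the centre strata. It also gives a P value without an adjusted difference and confidence interval, which is what a hypothesis-generating analysis most needs to report.

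The cytokine comparison deserves good precision because the Discussion proposes reduced surgical stress and immunosuppression as the route to fewer recurrences. IL-6 and IAP are the trial's direct look at that step.

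Time to functional recovery is a time-to-event outcome placed under a test for fully observed values. Patients who die or never recover have no observed time. If they were left out, the worst outcomes would vanish from the comparison, and an arm with more of them would look better than it should. The plan states no rule that prevents this.

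**Working it through.** The plan gives no power or precision figure for these outcomes, so there is none to reproduce. The check asks how much a baseline-adjusted analysis would gain.

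**Inputs.** From the Sample size section: 150 patients per arm (before the dropout allowance), two-sided 0.05, 80% power. From the Introduction: hospital mortality below 5%, a background figure for open major hepatectomy. Assumed, because the documents give neither: a baseline-to-follow-up correlation r of 0.3 to 0.7, and an effect of 0.3 SD.

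**Variance.** With baseline as a covariate, residual variance is 1 − r² of the unadjusted variance: 0.91 at r = 0.3, 0.75 at r = 0.5, 0.51 at r = 0.7. The reduction is thus 9%, 25% or 49%. At r = 0.2 it is 0.2² = 4%, and at r = 0.1 it is 1%.

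**Smallest detectable difference at 80% power.** For an unadjusted mean comparison: (1.960 + 0.842) × √(2/150) = 0.323 SD. Mann–Whitney has relative efficiency 3/π on normal data, giving 0.323/√(3/π) = 0.331 SD. ANCOVA gives 0.323 × √(1 − r²) = 0.309, 0.280 and 0.231 SD.

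**Power at 0.3 SD.** Simulation used normal data, one baseline and one follow-up value, 150 per arm and 2,000 runs per row. Centre was not simulated.

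| r | Mann–Whitney, follow-up value | Mann–Whitney, change | ANCOVA |
|---|---|---|---|
| 0.3 | 70% | 58% | 77% |
| 0.5 | 71% | 72% | 85% |
| 0.7 | 74% | 91% | 95% |

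Closed-form check: 0.3/√(2/150) = 2.598.

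- Mann–Whitney: 2.598 × √(3/π) = 2.539, and Φ(2.539 − 1.960) = 72% at any r. The spread of 70–74% is simulation noise.
- ANCOVA: 2.598/√(1 − r²) = 2.72, 3.00 and 3.64, giving 78%, 85% and 95%.

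The change-score column matters because the plan does not say which quantity is tested. Change scores have variance 2(1 − r) relative to the follow-up value: 1.4, 1.0 and 0.6. They lose power when r is below 0.5 and never reach ANCOVA in this range.

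**Functional recovery.** At the 5% ceiling, 0.05 × 150 = 7.5 deaths would be expected per arm. In 2,000 simulated trials per scenario, with identical recovery times in both arms, the rank test rejected as follows:

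| Deaths, arm 1 vs arm 2 | Deaths excluded | Deaths given worst rank |
|---|---|---|
| 5% vs 5% | 5.3% | 5.2% |
| 5% vs 2% | 5.0% | 7.7% |
| 5% vs 0% | 4.6% | 10.8% |

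With equal mortality the rule makes no difference. With unequal mortality, worst rank registers the excess deaths and exclusion hides them. The rule therefore decides what the comparison measures, and it is not stated.

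**The case against.** The strongest reply is that nothing confirmatory depends on this. Secondary outcomes are hypothesis-generating, the primary log-rank comparison is untouched, and a rank test is an ordinary choice for cytokines that may be skewed. This stands, and it sets the severity. It does not remove the point: the article names the method, and a baseline-adjusted model would replace it rather than fill in detail left to an analysis plan.

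The correlation is assumed, and one range is applied to both a questionnaire and cytokines after major surgery. That also stands. The gain could be near zero for one outcome and large for another.

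A reader might infer more than the documents support:

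- **That the comparison is biased or invalid.** It is not. Randomization protects an unadjusted test, and the loss is precision.
- **That baseline values are thrown away.** The text does not say whether follow-up values or changes are tested. In either case baseline is not used as a covariate.
- **That the test cannot deal with deaths, or that deaths will be dropped.** A rank test can place them last, and nothing says that they are excluded. What is missing is the rule.
- **That day-7 cytokine samples will be missing selectively in the laparoscopic arm.** The Discussion reports from earlier series that "Fewer wound and chest complications and shorter hospital stays are seen after LMH compared with OMH", but no length of stay or missing-sample rate is given. Day 7 is a scheduled time point listed separately from the day of discharge, and nothing limits sampling to inpatients. Missing samples would also affect any method of analysis.

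**Conclusion.** The point holds as a minor one, in two parts.

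First, the named test is valid but gives up precision on FACT-G, IL-6 and IAP that data already being collected could supply. At a 0.3 SD effect with 150 per arm, the loss against ANCOVA is about 6 to 22 percentage points of power for r between 0.3 and 0.7 (77 against 70, up to 95 against 74). These figures assume roughly normal outcomes, after log transformation for the cytokines, and a single follow-up value.

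Second, time to functional recovery needs a stated rule for patients who die or never recover. At the background mortality ceiling up to 7 or 8 deaths per 150 patients are involved. Non-recovery in survivors would add to that by an unknown number. Any distortion requires both that such patients be left out and that their proportion differ between arms; the documents establish neither.

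**What to change.** In the Statistical plan, restrict the Mann–Whitney test to continuous outcomes without a baseline value, such as operative time and blood loss, and add two provisions.

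1. Analyse FACT-G and log-transformed IL-6 and IAP by a linear mixed model over the post-surgery time points, or by ANCOVA at each time point, with the pre-surgery value and centre as covariates. Report adjusted differences with 95% confidence intervals.
2. For time to functional recovery, include all randomized patients, in line with the intention-to-treat commitment. Either give patients who die or never recover the worst rank and keep the Mann–Whitney test, or estimate cumulative incidence of recovery with death as a competing event and compare arms by Gray's test.

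The cost is a few sentences and some extra analysis; no new data are needed. Model assumptions must be checked on the log scale. A mixed model also relies on a missing-at-random assumption, which should be stated. The team should confirm that the named software, SPSS version 11.0, can run the chosen analyses.
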